#### Recruitment

Participants will be recruited by hospital- and community-based obstetricians in Cologne, Düsseldorf, and Bonn. To inform eligible women about the study, an information brochure with inclusion criteria and overall information will be used by hospital staff and obstetricians. If a woman shows interest, the recruiting centre will inform the project coordinator to contact her and provide further information about the randomization (intervention or control group). The date of the first enrolment was the 21st of June 2016. The recruitment is ongoing.

### Intervention

Depending on the place of recruitment, the nutrition counseling and exercise program will take place either in Cologne, Bonn or Düsseldorf in a conference room or at a gym, respectively. The intended group size will be 30 participants.

#### Nutrition counseling

Every nutrition counseling will be an extra appointment and is not part of the usual prenatal care appointments.

Pregnant women and their partners will be invited to a lecture about healthy diet during pregnancy at 8 weeks of gestation. This lecture will be followed-up by a 24 h dietary recall [38] to analyze individual energy intakes. This data will be entered and processed using the Prodi-Software® 6.2 (Science publishing society Stuttgart 2013, Germany) to calculate daily amounts of foods and nutrients. Based on this data, individual dietary counseling for the mother and, if possible, for the father will take place at 10 to 12 weeks of gestation. Individual counseling will be repeated at 16 and 24 weeks of gestation based on further 24 h dietary recalls. Additionally, group dietary counseling will consist of five sessions (weeks 14, 20, 30 and 36 of gestation, 8 weeks postpartum) and will be based on recommendations from the Network “Healthy Start – Young Family Network” [39]. Each session will last 60 min and will be led by a specially trained dietician.

After successful participation in the intervention, the families will receive a shopping voucher.

#### Exercise protocol

The exercise program is not part of the usual prenatal care appointments. From the 13th to at least the 36th week of gestation, women will carry out a supervised exercise program (aerobic exercise and strength training) twice a week for 90 min. Resting blood pressure will be measured in the first 10 min of each session before starting the exercise protocol. Every exercise session will include a 10–15 min gradual warm-up and a 10–15 min cool-down including low intensity calisthenics, relaxation and stretching (avoiding muscle pain) of most muscle groups (upper and lower limbs, shoulder and trunk) as well as 10 min of pelvic floor exercises. The main part of the session will last at least 40 min. Depending on the women’s condition, the main part will be devided into two to three parts of 20 or 15 min, respectively, with a little break in between the parts to avoid physical overload. The duration of the parts may be gradually increased as the intervention progresses.

Aerobic exercise sessions will consist of Nordic walking and walking. Each woman will wear a portable heart rate monitor (POLAR Electro Oy, Kempele, Finnland) during each session to stay within the recommended heart rate zone reported by Davenport et al. [40]. Furthermore, the talk test will be used to ensure that exercise is performed at moderate intensity [36].

Strength training will consist of exercises targeting major muscles groups in the upper body, trunk, and lower body by using resistance bands and light dumbbells. In total, the participants will perform two to three sets with 12–15 repetitions of 8–10 muscular strength exercises [41]. The workload and exercises will be documented for each woman on an exercise sheet. The intensity of the exercises will be set according to each woman’s perceived effort using the Borg scale [42]. Participants will progressively increase the resistance of each exercise. In addition, women will be encouraged to take up leisure-time activities such as walking for an additional 30 min per week to reach the recommended level of 210 min of exercise per week [36, 43].

### Control group

The intended group size will be 30 participants. Women allocated to the control group will neither be encouraged nor discouraged from exercising. They will undergo routine antenatal care and receive standard nutrition and activity guidelines from their obstetricians. To improve compliance, women from the control group will participate in a relaxation class, which includes breathing techniques and guided meditation once a week. The control group will undergo the same physical assessments as the intervention group.

#### Primary outcome

The primary outcome of this study will be the BMI of the infant at two years after birth assessed by German percentile [44].

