**Methods/design:**

A randomized multi-center controlled trial will be conducted in Germany, comparing supervised aerobic and resistance training 2x/week (13th to 36th weeks of gestation) and nutritional counseling (6th to 36th weeks of gestation) during pregnancy with usual care. Thirty women (pre-pregnancy Body Mass Index ≥25 kg/m^2^, 6th–10th week of gestation) will be included in each group. Maternal anthropometric and physical measurements as well as blood sampling will occur at the 6th–10th, 13th–14th, 21st-24th, and 36th week of gestation, at delivery as well as 8 weeks and 24 months postpartum. Neonatal measurements and umbilical blood sampling will be performed at birth. Maternal and infants’ weight development will be assessed every 6 months till 24 months postpartum. A difference in childhood BMI of 1 kg/m^2^ at the age of two years between both groups will be assumed. A power size of 80% using a significance level of 0.05 and an effect size of 1.0 is presumed.

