#### Sample size

Power analysis was done based on recommendations of weight gain in German children at 24 months after birth [37]. Normal weight gain (50th percentile) after subtraction of birth weight is nine kilograms at the age of 24 months. The BMI shows a difference of 1 kg/m^2^ at this time point (50th percentile). Therefore, a difference of 1 kg/m^2^ at the age of two years between the intervention and the control group will be assumed. To detect this difference in proportions with 80% power (GPower analysis) using a significance level of 0.05 and an effect size of 1.0, 48 women are needed. Calculating with a drop-out rate of 25% during the program, 60 women are required and planned to be recruited for this study.

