#### Follow-up

Infants’ weight, height, and head circumference will be obtained from examination records after 1, 4, 8, 12, and 24 months. The Ages and Stages Questionnaire (ASQ 3rd Edition) will be used to systematically screen the children for developmental and social-emotional delays in the crucial early years of life [51]. Five domains of development, including communication, gross motor, fine motor, problem-solving, and adaptive skills will be assessed through this questionnaire every four months (at 4, 8, 12, 16, 20, and 24 months postpartum). In conjunction with the questionnaire at 24 months, the Bayley Scale of infant and toddler development, 3rd edition (German version), will be used to assess motor (fine and gross) skills, language and cognitive development at this time point.

Furthermore, by using the Edinburgh Postnatal Depression Scale (EPDS Scale), postnatal depression will be recorded at weeks 6–8 after delivery [52]. In addition, questionnaires will be used to analyze maternal and paternal lifestyles after the intervention based on the German Health Interview and Examination Survey for Adults [53].

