#### Statistics

The main variable (BMI at 24 months) will be analyzed by covariance analyses evaluated by the factor group, breastfeeding, and smoking as well as covariances of parental age, paternal BMI, socioeconomic status, breastfeeding, and potential pregnancy-induced diseases (e.g. gestational diabetes mellitus, pregnancy-induced hypertension (PIH)). The significance level alpha will be set at < 0.05 for all analyses. All confidence intervals will be estimated at 95%. Missing data will be calculated according to the LVCF approach (Last Value Carried Forward). Analyses will be carried out as per-protocol-analyzes and intention-to-treat analyses (ITT). Spearman and Pearson correlation procedure will be used to assess relationships between maternal data (physical activity in METs, eating habits, weight gain, blood samples) and neonatal data (birth weight, length, head circumference, Apgar scores, cord blood sample) as well as infants’ development. Multiple linear regressions will be performed for neonatal measures to determine correlations with maternal and paternal lifestyle factors. The model will include group (intervention yes/no) as well as maternal and paternal characteristics as possible confounders. Explained variance (r-squared) for the linear regression model will be reported as model fit statistic.

Statistical analysis will be performed using SPSS 24.0 data-analysis software (Statistical Product and Service Solutions 24.0) and data analysis will be blinded.

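### The primary endpoint is not tied to one metric: BMI referred to a percentile in the outcome, a kg/m² difference mislabelled as proportions in the sample size, and BMI without infant sex or exact age in the analysis

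*Protocol article*

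**What the plan says.** Four sections of the protocol article bear on the metric.

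- **Primary outcome:** "The primary outcome of this study will be the BMI of the infant at two years after birth assessed by German percentile". It does not say whether the analysed value is kg/m², a percentile rank, an SDS or a percentile class. The reference cited is number 44.
- **Sample size:** "a difference of 1 kg/m^2^ at the age of two years between the intervention and the control group will be assumed". The next sentence begins "To detect this difference in proportions with 80% power (GPower analysis" and gives an alpha of 0.05, an effect size of 1.0 and 48 women. No SD, event, cut-off or rate appears. The growth reference cited here is number 37, not 44.
- **Statistics:** "The main variable (BMI at 24 months) will be analyzed by covariance analyses". The factors and covariates are group, breastfeeding, smoking, parental age, paternal BMI, socioeconomic status and pregnancy-induced diseases. Infant sex and exact age at measurement are not among them. Missing data are filled by last value carried forward.
- **Follow-up:** infant weight and height "will be obtained from examination records after 1, 4, 8, 12, and 24 months".

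The abstract restates the target without proportions: "A difference in childhood BMI of 1 kg/m^2^ at the age of two years between both groups will be assumed". The Discussion also speaks only of infants' BMI.

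**The concern.** The primary outcome, the sample size and the primary analysis should describe the same quantity. Here the outcome brings in a percentile that neither of the other two uses, and the sample size brings in proportions that nothing else supports. Three things follow.

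1. **Choice of test.** Raw BMI and a reference-standardised BMI are both defensible readings of the outcome and analysis sections. With about 48 evaluable children the two can give different answers, and the text does not say which is primary.
2. **Sex and age.** A percentile or SDS from a sex- and age-specific reference takes account of the child's sex and exact age. Raw BMI in the listed model does not, and the values come from routine records at a nominal age.
3. **Missing values.** On the Follow-up schedule the last possible value before 24 months is the one at 12 months. Carrying forward a raw BMI puts a one-year-old's value in place of a two-year-old's. Carrying forward an SDS assumes instead that the child keeps the same relative position. These are different imputations of the primary endpoint.

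**Working it through.** **Step 1. The plan's own figure on the kg/m² scale.** Inputs from Sample size: difference 1 kg/m², effect size 1.0, power 80%, alpha 0.05 (taken as two-sided), with 1:1 allocation from the design section. Read as a standardised mean difference, d = difference / SD, so 1.0 = 1 / SD and SD = 1.0 kg/m². The SD is not stated.

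- Normal approximation: n per arm = 2 × (1.960 + 0.842)² / 1.0² = 15.7, so 16.
- Two-sample t-test (noncentral t): 16.7, so 17 per arm and 34 in total.
- The stated 48 (24 per arm) is not reproduced. At d = 1.0 it gives 92.4% power. It gives 80% only at d = 0.826, that is SD = 1 / 0.826 = 1.21 kg/m².

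This mismatch is a separate matter. It is shown here because it means the SD behind the target cannot be recovered from the text.

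**Step 2. Does the word proportions fit?** A comparison of proportions needs two rates, and none is given. If effect size 1.0 is read as Cohen's h, with assumed control rates of 10% to 50%, the answer is 16 to 18 per arm, or 20 to 22 with continuity correction. That is 32 to 44 in total, so this reading does not give 48 either. The word fits neither the stated 1 kg/m² nor the covariance analysis.

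**Step 3. What a real dichotomy would mean.** With 24 per arm, 80% power needs these contrasts (lower rates assumed):

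| Lower rate | Higher rate needed | Difference |
|---|---|---|
| 10% | 46% | 36 points |
| 20% | 59% | 39 points |
| 30% | 70% | 40 points |
| 50% | 87% | 37 points |

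As an illustration, assume normal BMI, a cut at the reference 90th percentile (z = 1.28), controls centred at z = 1 and a 1 SD reduction. The shares above the cut are then 1 − Φ(0.28) = 38.9% and 1 − Φ(1.28) = 10.0%. The 28.9-point difference falls short of the 36 needed at a lower rate of 10%.

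**Step 4. Would continuous percentile rank change the required sample?** Assume normal BMI with SD 1.0 and a 1 SD reduction. Transform both arms to percentile rank and divide the mean difference by the pooled SD.

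| Control mean (z) | Effective d on percentile scale | n per arm, 80% power |
|---|---|---|
| 0 | 0.99 | 18 |
| 0.5 | 1.01 | 17 |
| 1.0 | 0.99 | 18 |

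Raw BMI needs 17. With SD 1.21 the figures are 25 to 26 against 24.

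**Step 5. Why the SD must be stated with the metric.** The same 1 kg/m² is 1 / 1.0 = 1.00 SD, 1 / 1.21 = 0.83 SD or 1 / 1.5 = 0.67 SD. The t-test then needs 17, 24 or 37 per arm, and 24 per arm gives 92.4%, 80.0% or 61.8% power. SDs other than the implied 1.0 are assumptions.

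**The case against.** The strongest reply is that the metric is clear enough. The abstract, the 1 kg/m² target, the Statistics section and the Discussion all use BMI, and the outcome sentence itself calls the outcome BMI. *Assessed by* a percentile may only mean judged against reference curves. On that view *proportions* is a slip, and the exact transformation can wait for the analysis plan. Much of this stands. A reader might infer that outcome, sample size and analysis use three different scales, but the documents do not establish that. A test of proportions does not fit the covariance analysis at all.

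Two further inferences fail. The first is that a percentile scale shrinks the planned effect about fourfold in the upper tail. A 1 SD rise from the 90th percentile is 8.9 points against 34.1 from the median, a ratio of 3.8. But the trial aims to lower BMI. A 1 SD fall takes the 90th percentile to about the 61st, 28.9 points against 34.1, a ratio of 1.2. The second is that the power figure does not carry over to percentiles. Step 4 shows that it nearly does.

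It is also fair that, under randomisation, leaving out sex and exact age costs precision and leaves chance imbalance uncorrected; it is not a systematic bias. Nor does the point call for moving the measurement to the 24-month developmental test, which would be a separate change to data collection.

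The reply does not remove the mismatch. *Proportions* is wrong as written, the percentile in the endpoint definition has no counterpart in the analysis, and two different growth references are cited. These are conflicts between statements the article makes, not detail left for later.

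**Conclusion.** The point holds as a failure to fix one metric for the primary endpoint, with one incorrect term in the power statement. It should be corrected, but it does not invalidate the design.

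Its size is modest if the endpoint stays continuous. Raw BMI and percentile rank need 17 against 17 to 18 per arm at d = 1.0, assuming normal BMI and control means between z = 0 and z = 1. It would be large only if the endpoint were dichotomised, where 24 per arm has 80% power only for differences of about 36 to 40 percentage points. The text gives no cut-off, so that is a reason to delete the word, not evidence that the trial is underpowered on this account.

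The practical gains from fixing the metric are a single pre-stated primary test, adjustment for sex and exact age, and a carried-forward value that is at least standardised for age. The documents give no figure from which the precision gain could be calculated.

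**What to change.** 1. **Primary outcome:** name one continuous metric, preferably BMI-SDS at 24 months for sex and exact age, from one named German reference. The sources cited cannot be seen here. If the chosen one gives no SDS parameters, use BMI in kg/m² and add infant sex and exact age at measurement to the covariates in Statistics.
2. **Statistics:** use that metric as the dependent variable, and as the value carried forward wherever last value carried forward is applied. Standardising removes the age mismatch but not the method's own assumption that the child's relative position stays constant.
3. **Sample size:** delete the words *in proportions*, and restate the target difference and its SD on the chosen metric, with 1 kg/m² as the translation for readers.
4. **Reporting:** give kg/m² and percentile class descriptively.

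The cost is a few sentences and a routine conversion, using the date of measurement and the child's sex and date of birth. The small downside is that SDS results must be translated into kg/m² for clinical readers.

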#### Secondary outcomes

Secondary outcomes will be assessed during pregnancy and postpartum and will include:
The course of pregnancy (weight gain according to the recommendations of the Institute of Medicine (IOM) [45], manifestation of pregnancy-induced diseases, mode of delivery)Anthropometric data of the mother and the father (weight, height, BMI, circumferences, body fat distribution)Anthropometric data and health status of the new-born (birthweight, length, head circumference, umbilical artery pH value, Apgar scores at one, five and ten minutes)Cord blood biomarkers in the newborn (insulin, leptin, adiponectin, resistin, BDNF, TNF-α, IL-6, CRP, fetuin A)Maternal and paternal biomarkers (insulin, leptin, adiponectin, resistin, BDNF, TNF-α, IL-6, CRP, fetuin A) during and after pregnancyMaternal cortisol level in the saliva at mid-pregnancyPostnatal depression (using the Edinburgh Depression Scale) 8 weeks after birthInfant development (age-appropriate development of fine and gross motor skills, communication, personal and social skills)

### Outcome measures

#### Maternal measurements

Maternal anthropometric measurements of weight, height, BMI, skinfolds, and mid-arm and mid-thigh circumference will be assessed prior to the start of the program (week 8 of gestation), at weeks 14, 24, and 36 of gestation, at 8 weeks postpartum, and at 12 and 24 months postpartum.

Maternal body weight will be measured to the nearest kg using a digital scale (Tanita Corp., Tokyo, Japan) with the participant wearing casual clothing and no shoes. Maternal weight gain will be defined as the difference between self-reported pre-pregnancy weight and the last weight recorded before delivery. The IOM recommendations [45] will be used to classify excessive weight gain. Height will be measured to the nearest 0.1 cm using a metal stadiometer. Mid-arm and mid-thigh circumference will be measured to the nearest 0.1 cm with a non-extensible, flexible tape on the right side of the body. Skinfold thickness will be assessed by an observer using a Harpenden skinfold caliper (John Bull British Indicators Ltd., Harpenden UK) with a constant pressure of 10 g/mm^2^. The procedure will be carefully standardized and each measurement will be made in triplicate on the right side of the body. Four points will be measured to the nearest 0.2 mm at the triceps, thigh, subscapular and suprailiac site; the results will be averaged and incorporated into the eq. [46] to estimate percent body fat [47].

#### Paternal measurements

Paternal anthropometric measurements of weight, height, BMI, skinfolds, and circumferences will be assessed prior to the start of the program (week 8 of gestation), after delivery at 8 weeks postpartum, as well as two years after delivery following the same procedures as described above.

#### Blood sample

Maternal serum profiles will be assessed at eight time points after an overnight fast (> 10 h): before (week 8 of gestation), during (weeks 14, 24, 36 week of gestation), and after the intervention (labor, and at 8, 12 and 24 weeks postpartum). Paternal serum profiles will be assessed at three time points after an overnight fast (> 10 h): before (week 8 of gestation) and after intervention (at 8 weeks and 24 months postpartum). Umbilical cord blood samples will be collected from the placental part of the umbilical cord immediately after clamping.

Maternal, paternal, and umbilical cord blood samples will each be collected into separate 7.5 ml Sarstedt® gel vacutainers. The samples will be centrifuged within the next four hours at 2500 x g for 10 min at 4 °C. After centrifugation, serum will be separated into 1.6 ml non-pyrogenic, non-mutagenic cryoPure aliquots and stored at − 80 °C until analysis. All samples will run in duplicates and in case of a coefficient of variation of > 5%, a third measurement will be performed.

Serum concentrations of glucose, total cholesterol, triglycerides, HDL-cholesterol, and LDL-cholesterol will be analyzed by colorimetry with a Cobas Integra analyzer (Roche Diagnostics, Germany) according to the manufacturer’s instructions. Insulin will be measured by radioimmunoassay (Roche Diagnostics Germany). Serum irisin and serum fetuin-A will be detected using a human ELISA kit (Phoenix Pharmaceutical, Burlingame, CA/USA; Epitope Diagnostics, San Diego, CA/USA). Adiponectin, CRP, leptin, resistin, BDNF and TNF-α will be investigated by a multiplex immunoassay (2Plex and 4Plex) from eBioscience according to the manufacturer’s instructions. Serum IL-6 will be analyzed using single high-sensitive human ELISA kit (eBioscience).

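### The maternal serum schedule contradicts itself after birth: the methods end at 24 weeks, the abstract at 24 months

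*Protocol article*

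**What the plan says.** The Blood sample section gives the number of maternal draws: "Maternal serum profiles will be assessed at eight time points after an overnight fast (> 10 h"). It lists the draws up to late pregnancy as "before (week 8 of gestation), during (weeks 14, 24, 36 week of gestation"). For the remaining four it gives this wording: "after the intervention (labor, and at 8, 12 and 24 weeks postpartum"). The next sentence of that section gives the fathers' later draws as "after intervention (at 8 weeks and 24 months postpartum").

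The abstract (Methods/design) puts maternal measurement and blood sampling in one list: "Maternal anthropometric and physical measurements as well as blood sampling will occur at the 6th–10th, 13th–14th, 21st-24th, and 36th week of gestation", then "at delivery as well as 8 weeks and 24 months postpartum". It adds that maternal and infant weight is assessed every 6 months up to 24 months.

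The Maternal measurements section sets postpartum anthropometry "at 8 weeks postpartum, and at 12 and 24 months postpartum". Under Follow-up, the infant's weight, height and "head circumference will be obtained from examination records after 1, 4, 8, 12, and 24 months".

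The Secondary outcomes section includes maternal and paternal biomarkers during and after pregnancy, without naming a postpartum time point.

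**The concern.** Two statements of one sampling schedule cannot both be followed. A centre working from the Blood sample section would take its last maternal sample about half a year after birth. A centre working from the abstract would take it at two years.

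Postpartum maternal biomarkers are a listed secondary outcome, and parental metabolic function is part of the study aim stated in the Background. If the methods text is followed, there is no maternal value at the time when fathers give blood, mothers are measured and the child's BMI is obtained. A sample not drawn on time cannot be recovered later. The trial runs at three hospitals and the article describes recruitment as ongoing, so the text could still affect draws to come.

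**Working it through.** No power or alpha calculation applies. The check is a count of time points and a comparison of the schedules.

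**1. The plan's own figure.** Blood sample section: 1 before (week 8) + 3 during (weeks 14, 24, 36) + 4 after (labor; 8, 12 and 24 weeks postpartum) = 8. This reproduces the stated eight.

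**2. The same count with the other unit.** If the last two draws are read as 12 and 24 months: 1 + 3 + 4 (labor, 8 weeks, 12 months, 24 months) = 8. The total is the same, so it cannot show which unit was meant.

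**3. The abstract.** 4 gestational windows + delivery + 8 weeks + 24 months = 7. There is no 12-week or 12-month draw. A change of unit in the Blood sample section would bring the last draw into line but would still leave 8 against 7.

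**4. Distance between the last draws.** At 4.345 weeks per month, 24 weeks / 4.345 = 5.5 months, and 24 − 5.5 = 18.5 months. Likewise 12 weeks / 4.345 = 2.8 months.

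**5. Postpartum schedules side by side (after delivery).**

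| Source | Time points |
|---|---|
| Maternal serum, Blood sample section | 8, 12, 24 weeks |
| Maternal measurement and blood, abstract | 8 weeks, 24 months |
| Maternal anthropometry, Maternal measurements section | 8 weeks, 12 months, 24 months |
| Paternal serum, Blood sample section | 8 weeks, 24 months |
| Infant records, Follow-up section | 1, 4, 8, 12, 24 months |
| Maternal and infant weight, abstract | every 6 months to 24 months |

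Of the three draws after delivery in the Blood sample section, one (8 weeks) coincides with a maternal anthropometry visit in the methods. Read as 8 weeks, 12 months and 24 months, all three would. The 12- and 24-week draws also match no paternal visit. The 24-week draw is, however, close to the abstract's 6-month weight assessment: 6 × 4.345 = 26.1 weeks, so about 2 weeks apart.

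**6. Which reading is likelier.** In pregnancy, the serum and maternal anthropometry schedules agree exactly (weeks 8, 14, 24, 36). They part only after birth, where the numerals 8, 12, 24 are the same and the unit differs. With the 24-month draws for mothers in the abstract and for fathers in the next sentence, this points to a slip for months. It does not prove one.

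**The case against.** The strongest reply is that this is a one-word slip with little consequence. The abstract states a 24-month maternal draw, the neighbouring schedules use months, and Fig. 2, which carries the schedule of assessments, is not reproduced in the text at hand and may give the right times. Centres may work from that figure or from the full protocol. All of this is fair, and it lowers the severity. It does not remove the contradiction, because the methods text is stated plainly and its own total of eight does not expose the error.

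The following stronger readings are tempting, but the documents do not support them:

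- **The trial chose to have no maternal serum at 24 months.** This is true only of the Blood sample section; the abstract states such a sample.
- **The 12- and 24-week draws match no assessment at all.** This holds against maternal anthropometry in the methods, the paternal visits and the infant records under Follow-up, but the 24-week draw lies near the abstract's 6-month weight assessment.
- **A planned analysis would be lost.** The Statistics section names no comparison of mothers with fathers at 24 months and no correlation of 24-month maternal serum with the child's BMI. Draws at 8, 12 and 24 weeks would also satisfy the literal wording of the secondary outcome.
- **Data have been or will be lost.** That depends on which document the centres use, which cannot be seen.

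The seven-against-eight count is also weak evidence of a second error. The abstract is condensed, and its combined list also leaves out the 12-month maternal visit.

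**Conclusion.** The maternal serum schedule is wrong as written, because the Blood sample section and the abstract cannot both be right about the last maternal draw. The gap is about 18 months: 24 weeks against 24 months. Maternal draws at 24 months number none in the one and one in the other.

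The matter is an internal inconsistency of moderate severity. It bears on the timing of postpartum samples for one secondary outcome. Infant BMI at two years, the sample size, the significance level and the covariance analysis do not depend on it.

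The contradiction follows from the text alone. Two further statements rest on assumptions. That the unit is a slip for months is an inference from the parallel schedules. That samples would be missed assumes that centres follow the methods text as printed.

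**What to change.** Reconcile the Blood sample section with the abstract, the Maternal measurements section and the schedule in Fig. 2:

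- Give one unit for each postpartum maternal draw, and one list and one total that agree wherever they appear.
- State whether there is a 12-month draw. The abstract has none, so changing weeks to months would not by itself align the two places.
- Keep the 24-month maternal sample that the abstract already states, unless the sponsor confirms that it was dropped; in that case correct the abstract.
- Tell the three centres which schedule applies before further postpartum draws.

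The cost is a line or two of text and a note to the centres. If the last two draws are in months, the number of draws in the Blood sample section stays at eight. Nothing in the sample size or the main analysis has to be redone.
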